#### *Exercise capacity (primary outcome)*

Exercise capacity is a well-established predictor of cardiovascular and overall mortality. Cardiopulmonary exercise testing (CPET) with determination of peak VO2 is the 'gold-standard' assessment of exercise capacity, that provided unique information on cardiovascular and ventilatory systems' responses, simultaneously, under precise conditions of metabolic stress. This makes CPET ideal non-invasive tool to establish the functional status of the heart, which provides a wealth of clinically relevant diagnostic and prognostic information.

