## 13. STATISTICAL CONSIDERATIONS

### 13.1 Analysis of Outcome Measures

Analysis will follow intention to treat principles (ITT) Following data cleaning, levels of demographics gathered at primary screening will be quantified using basic statistics (mean, SD, Median, IQR) and graphical presentations (boxplots, histograms, scatter plots) Sub division will be made by intervention /control and stratum. Likewise levels of primary and secondary outcomes at baseline will be similarly reported. Prior to any substantial analysis, preliminary impression of trends in longitudinal measurements will be provided graphically, separately for intervention and control participants.

1. Linear mixed model analysis will be used to compare peak  $VO_2$  at two years between the intervention and the control group Covariates will be baseline peak  $VO_2$ , age, gender systolic/diastolic blood pressure and BMI measured at baseline. GP practices or recruitment centres will be included as random effects to enable findings from this trial to be judged in the context of a different group of GP practices

2. Further exploratory analyses will incorporate interaction terms between intervention/control and each of the covariates. Backward elimination will be used to remove non significant interactions and then non significant main effects. If residuals from mixed model analysis violate the assumption of a normal distribution as tested by Kolmogorov Smirnov test then transformation of the dependent variable or bootstrap analysis will be conducted. Transformations considered will be those in the Box Cox family i.e. power and log. Bootstrap analysis will involve sampling with replacement 1000 sets of data from the original data, each of the same size as the original dataset Each set will then be analysed in the same manner as the original dataset This will enable an empirical distribution of each test statistic to be formed and relocated at its null hypothesis value Significance of the statistics in the original data will then be determined from the appropriate tail area of the empirical null distribution.

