Secondary analyses will also use linear or non linear mixed modelling as above but with dependent variable the secondary end points mentioned in the earlier Trial End Points section Interactions between intervention/control, and age and gender will also be included in the mixed modelling analyses to see whether differences in secondary endpoints between intervention and control participants vary with these two factors. Each mixed model analysis will be run additionally separately on each stratum. The primary QoL analysis will be the change in the overall QoL score between treatment groups over the two year duration. This will include baseline measures as a covariate. Full analysis will therefore be completed at the 24 months period and this will form the principle QoL analysis. The 12 month QoL assessments will allow a preliminary analysis to be undertaken to determine if changes occur within the first 12 months. These repeated measures will allow further exploratory analysis of changes in QoL to be undertaken to explore which domains are driving the changes in the QoL scores.

3. Missing values will be substituted using a multiple imputation procedure. Because of the likelihood of non normality the method of Hussain will be used. This replaces the data by its Normal scores, imputes using these transformed data and then uses a polynomial relationship between Normal scores and untransformed data to give a complete set of data. This is then repeated 10 times and variation seen between repetitions and within are used to estimate the uncertainty in the imputed mean value.

In the case of missing data due to death of the participant during the trial a comparative analysis will be conducted between surviving participants and the deceased. If no difference is apparent then MI will be performed on all of the data but otherwise a complete case analysis will be conducted and a report compiled setting out the difference between the deceased and the surviving participants.

|                          |            |               |            |       |          |
|--------------------------|------------|---------------|------------|-------|----------|
| Trial name:              | IMPRESS-AF |               |            |       |          |
| Protocol version number: | 6.0        | version date: | 12/10/2015 | Page: | 45 of 67 |

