### 13.1.1 Power Calculations

We will send invitations to 1280 potential participants from 64 GP practices with the aim of recruiting 640 for further testing. 250 of the screened participants will then be randomised. In addition, suitable participants from outpatient clinics run by [name] and [name] will also be invited to take part.

Our primary outcome will be based on a 'gold' standard test of exercise tolerance defined by peak  $\text{VO}_2$  using CPET and assessed at baseline and after the treatment with the trial drug. We hypothesise that the spironolactone will improve peak  $\text{VO}_2$  compared to the placebo treated subjects. We base our power calculation for peak  $\text{VO}_2$  on the published values of peak  $\text{VO}_2$  in subjects with HFpEF ( $16 \pm 5$  ml/min/kg). We anticipate a difference of 2ml/min/kg in the improvement in peak  $\text{VO}_2$  after 2-year treatment with spironolactone compared with the control group. Unfortunately this publication does not give a standard deviation on the change in peak  $\text{VO}_2$  from baseline but a similar trial, Edelmann et al provides that statistic (5 ml/min/kg) and also reports a similar magnitude of effect.

A sample size of 100 patients in each group will have 80% power to detect a difference in means of 2.000 assuming that the common standard deviation is 5.000 (effect size =0.40) using a two group t-test with a 0.05 two-sided significance level. Sample size calculation was conducted using the nQuery software. Approximately, for 80% power at 5% significance, sample size in each group would be  $15.68/(\text{effect size})^2$ . To accommodate a loss to follow-up of 20% of patients from each group would imply initially recruiting a total sample size of 250 ( $250 \times 0.8 = 200$ ) in order to still retain 200 patients in all. Loss of 20% of patients would still enable effects in excess of 2.3ml/min/kg (effect size=0.46) to be detected with 90% power at the 5% significance level. Sample size= $21.0/(\text{effect size})^2$  for 90% power, 5% significance. At the other extreme zero loss to follow up from 250 patients would lead to 88% power to detect a 2 ml/min/kg at 5% significance Prediction of 20% loss to follow up is based on a 10% loss per year and composed of 5% due to death and 5% due to other reasons. The relevant population of patients would be under regular follow up and as such would have relatively lower expected mortality.

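### Protocol 13.1 lets a comparison of deceased with surviving participants choose the missing-data method, and one branch imputes 24-month peak VO2 for people who have died

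*Protocol*

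**What the plan says.** Protocol section 13.1 compares peak VO2 "at two years between the intervention and the control group" with a linear mixed model. The covariates are baseline peak VO2, age, gender, blood pressure and BMI.

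Item 3 of the same section gives the default for missing data: "Missing values will be substituted using a multiple imputation procedure". The method is a normal-scores imputation repeated 10 times.

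A further paragraph deals with data missing because the participant died. In that case "a comparative analysis will be conducted between surviving participants and the deceased", and the result decides the method: "If no difference is apparent then MI will be performed on all of the data but otherwise a complete case analysis will be conducted". In the second case a report on how the two groups differ is also to be written.

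The paragraph does not name the primary endpoint. It exempts no endpoint either, so it applies to two-year peak VO2. It does not say which variables are compared or what would count as a difference.

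Section 13.1.1 plans for 10% loss a year, "composed of 5% due to death and 5% due to other reasons", and then remarks that mortality should be relatively low in patients under regular follow-up. The assessment table in section 8 places the exercise test (CPET) at baseline and month 24 only.

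**The concern.** The method for the primary endpoint depends on an observed comparison that says little about which method is appropriate.

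- **No difference apparent.** MI runs on all the data, including the dead. A participant who died before month 24 has no month-24 peak VO2. The imputed value describes a hypothetical in which that person lived and exercised, and the protocol never states that as its question. Failing to see a difference with few deaths is also weak evidence that there is none.
- **Difference apparent.** Complete-case analysis replaces MI. In its ordinary meaning this also drops imputation for participants who are alive but lack the final CPET. How the dead compare with survivors does not bear on whether to impute for the living.

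The background section gives a reason to expect a difference: "Exercise capacity is a well-established predictor of cardiovascular and overall mortality". Whether the trial sees it depends largely on how many participants die. At stake is which analysis set, and therefore which question, the primary result answers.

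**Working it through.** **1. The protocol's own figures.** Inputs from 13.1.1: difference 2 ml/min/kg, SD 5, effect size 2/5 = 0.40, two-sided 5% level, 100 per arm after 20% loss from 250.
- Protocol formula: 15.68/0.40² = 98 per arm. The normal formula gives 99.
- Noncentral t power: 80.4% with 100 per arm and 88.3% with 125 per arm.
- 250 × 0.8 = 200.

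These agree with the stated 80%, 88% and 250. The sample size is not in dispute.

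**2. How many participants the rule touches.**
- Deaths: 0.05 × 2 × 250 = 25. Compounded: 250 × (1 − 0.95²) = 24.4.
- Other losses at the same rate: about 25.
- MI branch: 250 analysed, with about 25 values created for the dead and about 25 for the living.
- Complete-case branch: about 200 analysed, so the roughly 25 living non-completers also lose the default imputation.

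Because the protocol expects relatively low mortality, I also take 12 deaths, about half the planned number. That lower figure is an assumption.

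**3. How well the comparison discriminates.** The protocol names no test. I assume a two-sided 5% t-test on one baseline variable, with all non-deceased participants as comparators. The noncentrality is d/√(1/n₁ + 1/n₂), with 248 degrees of freedom and critical value 1.970.
- 25 v 225: √(1/25 + 1/225) = 0.211. For d = 0.4 the noncentrality is 0.4/0.211 = 1.90 and the power is **47%**.
- 12 v 238: √(1/12 + 1/238) = 0.296. For d = 0.4 the noncentrality is 0.4/0.296 = 1.35 and the power is **27%**.

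Other differences with 25 deaths:
- 0.3 SD: 29%
- 0.5 SD: 66%
- 0.7 SD: 91%

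With 12 deaths, 0.5 SD is detected 39% of the time.

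The smallest difference detected with 80% power is (1.960 + 0.842) × 0.211 = 0.59 SD with 25 deaths. With 12 deaths it is 2.802 × 0.296 = 0.83 SD. On baseline peak VO2 with SD 5 these are about 3.0 and 4.1 ml/min/kg.

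So if the dead truly differed from survivors by 0.4 SD (2 ml/min/kg, numerically the trial's target effect), the rule would impute for them in about 53% of trials with 25 deaths and 73% with 12.

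**4. What these figures are.** They describe how often each branch is taken. They are not estimates of bias in the treatment effect.

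**The case against.** The strongest reply is that the switch may make little difference to the result. Only the final CPET is missing, and the model already adjusts for baseline peak VO2 and the other covariates. If missingness depends only on those, a complete-case analysis is valid and MI adds little. A simulation of the rule bears this out. It assumed 10% deaths related to baseline peak VO2 but not to arm, 10% other loss, and a baseline-to-final correlation of 0.5, which is not in the protocol. The mean estimate stayed within 0.03 ml/min/kg of the truth, type I error was close to 5%, and power was much the same as for complete cases. This stands. It does not cover deaths related to arm or missingness that the covariates do not explain.

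A second reply is that complete case may have been meant to exclude only the dead. That is possible, since the paragraph is about death, but it is not what is written.

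A third is that variables, test and threshold belong in a SAP. That is fair, and their absence is not the point here. A SAP that followed the protocol would still have to operate the switch.

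A reader might infer more than the documents support:
- **That the choice is post hoc.** The rule is written in advance, compares deceased with survivors and not arm with arm, and data analysts are blinded (section 6.3). It is data-dependent, but not readily steered by the treatment effect.
- **That it hides mortality.** Deaths are recorded as major adverse events, collected at visits (section 8.3) and reviewed with the SAEs by the DMEC (section 9.9). Imputing peak VO2 removes none of this.
- **That it contradicts the intention-to-treat statement.** That statement prescribes no missing-data method.
- **That chance alone would often trigger the switch.** Five independent tests at 5% would give 1 − 0.95⁵ = 22.6%, but the protocol specifies no such tests.

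**Conclusion.** The point holds as a fault in a rule that the protocol fixes. An observed comparison of deceased with survivors selects the missing-data method for every endpoint, including the primary one. One branch imputes a quantity that does not exist for about 10% of those randomised at the planned death rate. The other, read literally, withdraws imputation from about another 10%, who are alive, for an unrelated reason. The comparison detects a 0.4 SD difference 47% of the time with 25 deaths and 27% with 12.

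The detection figures assume one baseline variable, a two-sided 5% t-test and 12 to 25 deaths. The 10% shares use the protocol's rates without compounding.

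The documents do not show that the treatment effect would be biased by any particular amount. The case for change is that the primary question should not depend on this comparison, and that outcomes after death should not be imputed.

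**What to change.** Delete the survivor-versus-deceased switch from section 13.1 and fix one rule before unblinding:

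- Use MI for participants alive at 24 months without a CPET.
- Do not impute peak VO2 after death.
- Report deaths by arm beside the primary result.
- State that the primary estimate is among survivors.
- Add one prespecified sensitivity analysis that includes deaths, for example a rank-based comparison with death ranked worst.
- Keep complete-case analysis as a further sensitivity analysis.

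The comparison of deceased with survivors can stay as a descriptive report, provided that it decides nothing.

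The cost is a few sentences and one or two extra sensitivity analyses, with no new data or participants. The real downside is that the primary estimate conditions on survival, which is a post-randomisation event. The arms compared may then differ if treatment affects mortality. That is why the deaths by arm and the analysis that includes deaths belong with it. Ranking death worst is one choice among several, and what matters is that it is fixed in advance.

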### 13.1.1 Power Calculations

We will send invitations to 1280 potential participants from 64 GP practices with the aim of recruiting 640 for further testing. 250 of the screened participants will then be randomised. In addition, suitable participants from outpatient clinics run by [name] and [name] will also be invited to take part.

Our primary outcome will be based on a 'gold' standard test of exercise tolerance defined by peak  $\text{VO}_2$  using CPET and assessed at baseline and after the treatment with the trial drug. We hypothesise that the spironolactone will improve peak  $\text{VO}_2$  compared to the placebo treated subjects. We base our power calculation for peak  $\text{VO}_2$  on the published values of peak  $\text{VO}_2$  in subjects with HFpEF ( $16 \pm 5$  ml/min/kg). We anticipate a difference of 2ml/min/kg in the improvement in peak  $\text{VO}_2$  after 2-year treatment with spironolactone compared with the control group. Unfortunately this publication does not give a standard deviation on the change in peak  $\text{VO}_2$  from baseline but a similar trial, Edelmann et al provides that statistic (5 ml/min/kg) and also reports a similar magnitude of effect.

A sample size of 100 patients in each group will have 80% power to detect a difference in means of 2.000 assuming that the common standard deviation is 5.000 (effect size =0.40) using a two group t-test with a 0.05 two-sided significance level. Sample size calculation was conducted using the nQuery software. Approximately, for 80% power at 5% significance, sample size in each group would be  $15.68/(\text{effect size})^2$ . To accommodate a loss to follow-up of 20% of patients from each group would imply initially recruiting a total sample size of 250 ( $250 \times 0.8 = 200$ ) in order to still retain 200 patients in all. Loss of 20% of patients would still enable effects in excess of 2.3ml/min/kg (effect size=0.46) to be detected with 90% power at the 5% significance level. Sample size= $21.0/(\text{effect size})^2$  for 90% power, 5% significance. At the other extreme zero loss to follow up from 250 patients would lead to 88% power to detect a 2 ml/min/kg at 5% significance Prediction of 20% loss to follow up is based on a 10% loss per year and composed of 5% due to death and 5% due to other reasons. The relevant population of patients would be under regular follow up and as such would have relatively lower expected mortality.

Considering the power available for secondary endpoints, Conraads et al (the ELANDD trial) give sufficient statistical information to investigate this issue for 6 minute walk distance. Comparing the difference in change from baseline between a control group (n=59) and an intervention group (n=57) using nebivolol (26m difference), gave a t statistic p value of .004. This combination of t statistic and difference between groups implies an SD on change from baseline of 48m and a power of 96% to detect a 26m difference with a sample size of 100 in each group. With our larger sample size (n=100) in each group, a smaller difference of around 18m between the two groups could be detected with 80% power for 5% significance.

Returning to Edelmann et al they supply a 95% confidence interval on the difference between two groups in change from baseline for E/e'. This confidence interval (-4.3 to -2.1) together with the mean difference (-3.2) allows estimation of the SD for change from baseline in E/e'. (SD=2.08) In turn that enables a power calculation to be performed which reveals in excess of 99% power to detect a -3.2 difference in change from baseline between intervention and control group with our sample size of 100 in each group.

From the same paper and following the same steps (95% confidence interval -11 to 1 and mean difference -5) leads to an SD of 11.35 for change from baseline) In turn that suggests 87% power for MLWHFQ showing at 5% significance a difference in change from baseline of 5 units.

As well as influencing power, sample size influences precision of estimation. The 95% confidence intervals in the table indicate the precision of the mean endpoint (difference between intervention and control in change from baseline to two years). None of the confidence intervals contain zero indicating a significant effect of the intervention

|                          |            |               |            |       |          |
|--------------------------|------------|---------------|------------|-------|----------|
| Trial name:              | IMPRESS-AF |               |            |       |          |
| Protocol version number: | 6.0        | version date: | 12/10/2015 | Page: | 46 of 67 |

| Endpoint             | Mean endpoint | SD endpoint | SE endpoint | Lower 95%CI | Upper 95%CI |
|----------------------|---------------|-------------|-------------|-------------|-------------|
| Peak VO 2 | 2             | 5.00        | 0.71        | 0.61        | 3.39        |
| 6MWT                 | 26            | 48.00       | 6.79        | 12.70       | 39.30       |
| E/e'                 | -3.2          | 2.08        | 0.29        | -3.78       | -2.62       |
| MLWHFQ               | 5             | 11.35       | 1.61        | 1.85        | 8.15        |

Based on published data in similar populations treated according to current practice the annual rate of all cause hospital admissions ranges from 20% to 45%. For the power calculation we used a more conservative estimate of ~20% annual admission rate. The suggested conservative admission rate would allow detecting any significant reduction  $\geq 15\%$  in all-cause admissions in the treatment group vs. placebo group with 80% power and 5% significance. For comparing two rates  $R_1$  and  $R_2$  an approximate formula for sample size  $n$  would be:  $n = 7.84 \times (R_1 + R_2) / (R_1 - R_2)^2$ .

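### The protocol's own SD and sample size give about 75% power, not 80%, for an 18 m difference in 6-minute walk distance; the difference detectable with 80% power is about 19 m

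*Protocol*

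**What the plan says.** Section 13.1.1 (Power Calculations) takes its 6-minute walk figures from an earlier nebivolol trial. The contrast drawn there, "between a control group (n=59) and an intervention group (n=57) using nebivolol (26m difference), gave a t statistic p value of .004", is the source of the SD: the protocol says that it "implies an SD on change from baseline of 48m". With that SD and 100 per group it reports 96% power for 26 m. It then adds, for the same 100 per group, that "a smaller difference of around 18m between the two groups could be detected with 80% power for 5% significance".

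Three other statements in the same section bear on this:

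- The primary-endpoint calculation is made "using a two group t-test with a 0.05 two-sided significance level". It finds that 100 per group gives 80% power at an effect size of 0.40.
- The approximate sample size per group for 80% power at 5% significance is given as 15.68 divided by the squared effect size.
- The precision table lists SD 48.00 m and SE 6.79 m for the 6-minute walk test.

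**The concern.** An 18 m difference with an SD of 48 m is an effect size of 18/48 = 0.375. A few lines earlier the same section says that 100 per group gives 80% power at 0.40. Both cannot hold for the same test and the same number of patients, because the smaller effect must have lower power.

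The sentence tells a reader how small a walking-distance difference the trial could pick up on the first-listed secondary outcome. As written it is slightly optimistic: under the stated calculation, a true difference of 18 m would be missed about 25% of the time rather than 20%.

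**Working it through.** **Inputs (all from section 13.1.1).** SD of change 48 m; 100 per group, equal allocation; 5% significance. The two-sided two-group t-test is stated for the primary endpoint and is assumed to apply here too. The 100 per group is already net of the 20% loss to follow-up (250 x 0.8 = 200).

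**Step 1: reproduce the SD.** With 59 and 57 patients there are 114 degrees of freedom, and a two-sided p of .004 corresponds to t = 2.938.

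SD = 26 / (2.938 x sqrt(1/59 + 1/57)) = 26 / (2.938 x 0.1857) = 47.65 m, which rounds to 48 m. Reproduced.

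**Step 2: reproduce the SE and the 96%.** SE = 48 x sqrt(2/100) = 6.79 m, as tabulated. For 26 m, 26/6.79 = 3.83 and the normal approximation gives Φ(3.83 − 1.96) = 96.9%; the exact t calculation gives 96.8%. The stated 96% is reproduced to within a point, so inputs and method have been read correctly.

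**Step 3: the 18 m figure.** 18/6.79 = 2.65, and Φ(2.65 − 1.96) = 75.5%. The exact noncentral-t power is 75.1%. The stated 80% is not reproduced.

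**Step 4: the difference detectable with 80% power.**

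| Route | Difference |
|---|---|
| Protocol formula: 48 x sqrt(15.68/100) | 19.0 m |
| Normal approximation | 19.0 m |
| Exact t | 19.1 m |
| Protocol's effect size of 0.40: 0.40 x 48 | 19.2 m |

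**Step 5: could another reading give 80% at 18 m?**

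| Reading | Power (normal and exact t) |
|---|---|
| SD 47.4 m, slightly below the unrounded 47.65 m | 76.2% to 76.6% |
| Difference 18.49 m (the largest that rounds to 18), SD 48 m | 77.4% to 77.8% |
| One-sided 5%, SD 48 m | 84.1% to 84.3% |
| 125 per group (no dropout), SD 48 m | 84.0% to 84.2% |

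None gives 80%. With 125 per group the protocol's formula gives a detectable difference of 48 x sqrt(15.68/125) = 17.0 m, so the 18 m is not the no-dropout figure either.

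**The case against.** The strongest reply is that this is trivial: the text says around 18 m, the gap is about 1 m, and the SD is itself back-calculated from rounded figures. If the source p-value lay anywhere from .0035 to .0045 and the source difference from 25.5 to 26.5 m, the SD could be 46.0 to 49.2 m and the difference detectable with 80% power 18.3 to 19.6 m. The low end rounds to 18.

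Part of this stands. The discrepancy is no larger than the imprecision of the source data. But the protocol fixes the SD at 48 m and uses it for the 96% and for the precision table. From 48 m the answer is 19 m, and the word around does not turn 19 into 18. Even the most favourable corner, SD 46.0 m, gives 78.6% for exactly 18 m.

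A reader might also infer three stronger things, none of which the document supports:

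- **That the trial has only 75% power for this endpoint.** The 75% belongs to the stated unadjusted t-test on change with 100 evaluable per group. Section 13.1 plans mixed models with covariates, and the primary model includes the baseline value. Assuming equal variances at both visits and adjustment for baseline only, 80% for 18 m needs a residual SD of about 45.2 m, which is met if the baseline to 24-month correlation is at most 2 x (45.2/48)^2 − 1 = 0.77. The protocol does not give that correlation, so the power of the planned analysis is not known from it.
- **That the trial is too small.** By the protocol's formula, 80% power for 18 m would take 15.68/0.375^2 = 111.5, so 112 per group. But 18 m is not a design target; the sample size rests on peak VO2.
- **That the closing claim of at least 80% power for secondary endpoints fails.** That claim is limited to differences in line with published results. For this endpoint the published difference is 26 m, where the power is about 97%.

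**Conclusion.** The sentence is wrong as written. On the protocol's SD of 48 m, 100 evaluable patients per group and a two-sided 5% two-group t-test, power for 18 m is about 75%, an overstatement of 4.5 to 5 percentage points. Put as a distance, the figure should be about 19 m rather than 18 m.

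The conclusion rests on carrying the two-sided t-test over from the primary endpoint; a one-sided test would not restore the stated figure. The error is minor and confined to this remark. The 96% for 26 m, the sample size, the planned analysis and, for this endpoint, the section's conclusion on power all stand.

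**What to change.** In section 13.1.1, replace 18 m with 19 m, so that the sentence says a smaller difference of around 19 m could be detected with 80% power at 5% significance. If the 18 m figure is worth keeping, add in brackets that it has about 75% power under the same calculation. Stating that the calculation is a two-sided t-test with 100 evaluable per group would make it checkable.

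The cost is one corrected number. Sample size, conduct and analysis do not change.

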#### *Sample size – calculations and conclusions*

We estimate that a sample size of 100 participants in each arm would give power of at least 80% to detect differences in primary and secondary endpoints of a magnitude consistent with published results from similar studies. Inclusion of provision for a 20% drop out rate could potentially lead to powers of near 90% or more if the assumption of a drop rate of 20% was too pessimistic.

|                          |            |               |            |       |          |
|--------------------------|------------|---------------|------------|-------|----------|
| Trial name:              | IMPRESS-AF |               |            |       |          |
| Protocol version number: | 6.0        | version date: | 12/10/2015 | Page: | 47 of 67 |

---

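### The 80% power stated for a 15% or greater reduction in hospital admissions gives no scale, comparator rate or time base; as a relative reduction its own formula gives about 8% to 12%, and only a fall from 20% to 5% a year meets the claim

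*Protocol*

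**What the plan says.** All-cause hospitalisation is a named secondary outcome. Section 2.2(d) defines it over the two-year follow-up.

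Section 13.1.1 cites published annual admission rates from 20% to 45% and then chooses the lower end: "For the power calculation we used a more conservative estimate of ~20% annual admission rate". It says that a reduction of 15% or more "in all-cause admissions in the treatment group vs. placebo group with 80% power and 5% significance" could be detected, and prints the approximate formula n = 7.84(R1 + R2)/(R1 − R2)². It gives no value for R2, does not say whether 15% is relative or absolute, and does not say whether R1 and R2 are annual or two-year rates.

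The closing paragraph on sample size says that 100 participants per arm "would give power of at least 80% to detect differences in primary and secondary endpoints", and limits this to effects in line with those reported by similar studies.

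For the six-minute walk test, section 13.1.1 says that with 100 per group "a smaller difference of around 18m between the two groups could be detected with 80% power for 5% significance".

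**The concern.** A reduction of 15% or more in admissions is most naturally read as a relative reduction. From a base of 20% a year that is a fall to 17%. A trial with 100 per arm cannot detect so small a difference in a rate with 80% power, and the formula printed beside the claim shows this.

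The stake is what the hospitalisation result can be expected to show. The protocol tells its readers that this secondary outcome is adequately powered for a modest effect. In fact it is powered only for a reduction of about half or more.

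**Working it through.** **Inputs, all from the protocol.** Control rate 0.20 per patient-year, so 0.40 per patient over two years (section 13.1.1 for the rate, section 2.2(d) for the period). 100 per arm after 20% loss, or 125 per arm with no loss. The constant 7.84 is (1.96 + 0.84)², that is, 80% power at a two-sided 5% level. This agrees with the primary calculation, which is made "using a two group t-test with a 0.05 two-sided significance level".

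**Formulas.** Required number per arm: n = 7.84(R1 + R2)/(R1 − R2)². Inverted for power: z = (R1 − R2)/√((R1 + R2)/n), and power = Φ(z − 1.96) + Φ(−z − 1.96).

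**The plan's own figure.** With R1 = 0.20, R2 = 0.05: n = 7.84 × 0.25/0.15² = 87 per arm. At 100 per arm z = 0.15/√(0.25/100) = 3.00, so power is 85%. With R1 = 0.20 and n = 100 the smallest detectable difference is 14.2 points (0.20 to 0.058). This is very probably the source of the 15%.

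**Every reading of the 15%.**

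| Reading | R1 to R2 | n per arm for 80% | Power at 100 per arm | Power at 125 per arm |
|---|---|---|---|---|
| Relative, annual rates | 0.20 to 0.17 | 7.84 × 0.37/0.03² = 3,223 | 7.8% | 8.5% |
| Relative, two-year rates | 0.40 to 0.34 | 7.84 × 0.74/0.06² = 1,612 | 10.7% | 12.2% |
| 15 points, two-year rates | 0.40 to 0.25 | 7.84 × 0.65/0.15² = 226 | 46% | 55% |
| 15 points, annual rates | 0.20 to 0.05 | 7.84 × 0.25/0.15² = 87 | 85% | 92% |

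Only the last row reaches 80%. It is a relative reduction of 0.15/0.20 = 75%, and it uses one year of a two-year outcome.

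**Sensitivity of the relative reading.**
- Comparing proportions instead of rates gives 8% to 16% power two-sided, and at most 25% one-sided.
- At the top of the quoted range, 45% a year (0.90 to 0.765 over two years), power is 18% at 100 per arm.
- Counting person-time before loss: assume 125 per arm and an even 10% loss per year. Then 125 × 0.95 + 125 × 0.85 = 225 person-years per arm, and power is 11.5%.

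**What the trial can detect over two years.** Solving (0.40 − x)² = (7.84/n)(0.40 + x):
- n = 100: x = 0.186, a 54% relative reduction (20% to 9.3% a year).
- n = 125: x = 0.205, a 49% relative reduction (20% to 10.3% a year).
- 225 person-years per arm: 20% to 9.8% a year, a 51% relative reduction.

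A true halving (0.40 to 0.20) has 73% power at 100 per arm and 82% at 125.

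**Six-minute walk test.** With SD 48 m, 15.68/(18/48)² = 111.5 per group are needed for 18 m. At 100 per group a t-test has 75% power for 18 m, and 80% power is reached at 48 × √(15.68/100) = 19.0 m.

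**The case against.** The strongest defence is that the stated figure does reproduce. The protocol never uses the word relative, its rate is a percentage per year, and its formula works on the absolute difference R1 − R2. On that basis 15 points off 20% a year has 85% power with 100 per arm. This stands: a reader might infer a plain arithmetic error, and the documents do not support that. The fault is the missing scale, comparator rate and time base. As a result, the natural reading is far from 80%, and the reading that works implies a 75% reduction that the text does not disclose.

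Three other stronger readings also go too far.

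- A reader might infer that nothing short of a fall from 20% to 5% a year is detectable. That is true only of the ways to read the 15%. Over the full two years, 80% power is reached at about 9% to 10% a year.
- A reader might infer that the closing statement promises 80% power for a 15% reduction. It does not, because it is limited to effects seen in similar studies. It is still unsupported for admissions, since the published sources cited there give a rate of admission and no treatment effect on it.
- A reader might infer that a null result will be taken to exclude a 15% reduction. The protocol contains no such rule of interpretation.

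The walk-test point is a slip of about 1 m in a figure stated as approximate. The 26 m claim is unaffected, and this slip adds no weight to the main point.

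**Conclusion.** The concern holds in this form. As written, the admissions claim cannot be evaluated without guessing the scale and time base. On its natural relative reading, power is about 8% (annual rates) to 11–12% (two-year rates, 100 to 125 per arm), not 80%. Fifteen points off the two-year rate has 46% to 55%. Only 20% to 5% a year meets the claim, and that is not the outcome defined in section 2.2(d).

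These figures rest on the protocol's 0.20 per patient-year and on the Poisson variance in its formula. Repeat admissions by the same patients would add variance and lower the power further.

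The text should be corrected, but the point does not threaten the trial. The sample size is set by peak VO2, and nothing in conduct, endpoint or analysis changes.

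**What to change.** In section 13.1.1, state the scale, R2 and the time base, and replace the admissions claim with wording such as:

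> At 0.20 admissions per patient-year over two years, 80% power is reached for a relative reduction of about 49% to 54% (from 0.40 to about 0.21 to 0.19 admissions per patient, with 125 to 100 per arm), before any allowance for overdispersion from repeat admissions. Power for a 15% relative reduction is about 11% to 12%.

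In the concluding paragraph on sample size, limit the statement of at least 80% power to the endpoints for which a calculation is shown. Admissions do not qualify as the text stands, and section 13.1.1 gives no calculation for EQ-5D or sinus rhythm.

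In the same edit, as a minor correction, change the walk-test figure from about 18 m to about 19 m.

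The cost is protocol wording only. The stated figures for admissions become less favourable, and sample size and conduct are unchanged.
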